#### 8.5 Replacement of individual subjects after withdrawal

Withdrawn participants will be replaced in order to attain the desired sample size.

#### 8.6 Follow-up of subjects withdrawn from treatment

Withdrawn patients will be followed for SAEs until 6 months after inclusion.

Participants withdrawn for medical reasons will be followed until the interfering condition has resolved or reached a stable state.

#### 8.7 Premature termination of the study

In case of multiple SUSARS the study will be terminated.

## **9. SAFETY REPORTING**

### **9.1 Temporary halt for reasons of subject safety**

In accordance to section 10, subsection 4, of the WMO, the sponsor will suspend the study if there is sufficient ground that continuation of the study will jeopardize participants' health or safety. The sponsor will notify the accredited METC without undue delay of a temporary halt including the reason for such an action. The study will be suspended pending a further positive decision by the accredited METC. The investigator will take care that all participants are kept informed.

Deblinding of subjects can be done by [name] and [name], both researchers in the experimental vascular medicine department that are fully independent of this study.

### **9.2 AEs, and SAEs**

#### **9.2.1 Adverse events (AEs)**

Adverse events are defined as any undesirable experience occurring to a individual during the study, whether or not considered related to [the investigational product / trial procedure/ the experimental intervention].

An event that is part of the natural course of the disease under study is captured in the study as a clinical activity measure. However, any specific symptoms or sequelae of the disease evolution (e.g., organ failure, respiratory distress) will be considered AEs. Clinically significant changes in laboratory values, blood pressure and pulse will not necessarily be reported as AEs. However, abnormal AEs that constitute an SAE or lead to discontinuation of administration of study drug must be reported and recorded as an AE.

The investigator is responsible for reviewing laboratory test results and determining whether an abnormal value in an individual study subject represents a change from values before the study. In general, abnormal laboratory findings without clinical significance (based on the Investigator's judgment) should not be recorded as AEs; however, laboratory value changes requiring therapy or adjustment in prior therapy should be considered AEs.

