#### *Blood withdrawal*

Blood will be collected at baseline, 8, 16 and 24 weeks. At baseline and 24 weeks, blood will be investigated on common liver enzymes, indicators of glycemic control, lipids, and general and more NASH-specific parameters. Blood withdrawal on 8 and 16 week is for safety and in a lesser extent for study purposes (e.g. enhanced liver fibrosis-panel).

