#### **9.2.4 Recording of AEs/SAEs**

All SAEs must be reported on the SAE form in the eCRF.

All SAEs that occur after the participant has signed the ICF up to 30 days after the last administration of the last investigational product will be reported. All non-serious AEs that are possibly related to the study are collected from randomization until 30 days after the last visit (at 24 weeks). All SAEs must be reported on the SAE form in the eCRF.

NCI CTCAE (National Cancer Institute; Common Terminology Criteria for Adverse Events) grading is used in haem/onc and refers to mild (G1) moderate (G2), severe (G3), life-threatening (G4), or dead (G5); currently v5.0 is used.

Participants with an AE of Grade > 1 will be further followed until the resolution of the AE to CTCAE Grade 0-1 or until initiation of a new therapy, whichever occurs first.

Participants with an adverse drug reaction (ADR) ongoing at EAPV must be followed until the ADR resolves, becomes stable, or is considered not clinically significant by the investigator.

A Data Safety Monitoring Board (DSMB) will be established to assess safety data, monitor trial integrity and make recommendations to the Sponsor.

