#### **9.2.5 Relationship**

The relationship or association of the study medication in causing or contributing to the AE will be characterized by the Investigator using the following classification and criteria:

- Possibly or probably related: A clinical event, including laboratory test abnormality, with a reasonable time sequence to study medication administration that might or might not be also explained by concurrent disease or other drugs or chemicals.
- Not related: A clinical event, including laboratory test abnormality, judged to be clearly and incontrovertibly due to extraneous causes (e.g., diseases, environment), or with a temporal relationship to study medication administration that makes a causal relationship improbable, and/or for which other drugs, chemicals, or underlying diseases provide a much more plausible explanation.

If applicable, the relationship of the AE to the study medication will be assessed by means of the question: "Is there a reasonable possibility that the event may have been caused by the investigational product?" The Investigator should respond to this question with either "Yes" or "No" separately for each study medication.

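### Section 9.2.1 makes recording of clinically significant laboratory changes as AEs optional in one paragraph, while the next leaves out only the non-significant ones

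*Protocol*

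**What the plan says.** Protocol section 9.2.1 opens with a broad definition: "Adverse events are defined as any undesirable experience occurring to a individual during the study".

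Its second paragraph then narrows this for measured values: "Clinically significant changes in laboratory values, blood pressure and pulse will not necessarily be reported as AEs". The exception follows at once: "abnormal AEs that constitute an SAE or lead to discontinuation of administration of study drug must be reported and recorded as an AE".

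Its third paragraph deals with laboratory results only. It leaves some out: "abnormal laboratory findings without clinical significance (based on the Investigator's judgment) should not be recorded as AEs". It brings others in: "laboratory value changes requiring therapy or adjustment in prior therapy should be considered AEs".

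Three other places bear on the point:
- Section 8.3, under Blood withdrawal, gives the purpose of the mid-treatment samples: "Blood withdrawal on 8 and 16 week is for safety", and only to a lesser extent for research.
- Section 9.2.4 restricts which non-serious events are collected: "All non-serious AEs that are possibly related to the study are collected from randomization until 30 days after the last visit (at 24 weeks".
- Section 9.2.5 defines possible or probable relationship for "A clinical event, including laboratory test abnormality, with a reasonable time sequence to study medication administration", so a laboratory abnormality is something whose cause the investigator may have to rate.

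**The concern.** The two paragraphs use clinical significance in opposite ways. In the third, lack of clinical significance is the reason to leave a laboratory finding out. In the second, clinical significance is not enough to bring one in. An investigator holding the same result can therefore record it or not, depending on which paragraph is followed.

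What is at stake is the handling of the individual event as well as its count. Under 9.2.4, AEs above CTCAE grade 1 are followed until they return to grade 0-1 or new therapy starts. Under 9.3, all AEs are followed until they abate or stabilise. A change that is never recorded as an AE has no such rule attached. This matters in a liver trial whose week 8 and 16 samples are taken mainly for safety, and in which section 6.5 concedes that the combination of the three strains has not been well studied.

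**Working it through.** No figure in the protocol can be reproduced here, and no arithmetic decides the point. The check is to take each kind of change and read it under both paragraphs. The exception in the second paragraph literally speaks of AEs rather than of changes; it is read here as referring to the changes just named.

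| Kind of change | Second paragraph of 9.2.1 | Third paragraph of 9.2.1 | Result |
|---|---|---|---|
| Laboratory change that is an SAE or stops study drug | Must be recorded | Nothing to the contrary | Agree |
| Laboratory change needing new or altered treatment, not an SAE, study drug continues | Recording optional | Counts as an AE | Explicit conflict |
| Clinically significant laboratory change, not serious, no treatment, study drug continues | Recording optional | Not among those left out | Conflict by implication |
| Laboratory change without clinical significance | Not addressed | Not recorded | No conflict |
| Clinically significant blood pressure or pulse change, not an SAE, study drug continues | Recording optional | Not addressed | Permissive rule only |

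Next, does another section settle rows two, three and five?

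1. The opening definition in 9.2.1 is broad enough to include all three, which favours the third paragraph, but the second paragraph is a specific carve-out from it.
2. Section 9.2.5 shows that laboratory abnormalities can be events. It classifies relationship and does not say which abnormalities are to be recorded.
3. Section 9.2.4 filters non-serious AEs by possible relationship. It works on events already regarded as AEs and does not choose between the paragraphs.
4. Section 8.4.1 withdraws participants whose new condition requires a change in drug prescriptions. Many cases in row two would then stop study drug and move to row one. The section does not reach treatment without a prescription change, and it does nothing for rows three and five.
5. Sections 9.2.6 and 9.3 cover grading and follow-up once an AE exists.

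No section reconciles the two paragraphs. A clinically significant week 8 or 16 result in row three can be left out by someone following the second paragraph as written.

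**The case against.** The best defence is that the paragraphs form one graded rule: not significant, leave out; significant, use judgement; treatment, SAE or stopping of study drug, record. The second paragraph is permissive, and the third never says that every significant finding must be recorded. This holds to the extent that row three is a conflict by implication only. It does not remove row two, where one paragraph makes recording optional and the other calls the event an AE. It also leaves row three to individual judgement without saying so.

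The sentence also follows text that treats natural-course events as disease activity measures, which could explain leniency about liver tests in NASH. But the sentence covers all laboratory values, blood pressure and pulse, so that explanation is too narrow. It may be a slip for changes that are not clinically significant; nothing in the protocol shows this, and the correction would be as simple.

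Several stronger readings are tempting, and the protocol does not support them:
- *That the contradiction extends to blood pressure and pulse.* The third paragraph speaks of laboratory findings only.
- *That the safety signal is lost.* Liver enzymes are named secondary outcomes in 8.1.3, and the Summary lists them for blood taken at baseline and weeks 8, 16 and 24. The values exist as data however the event is coded.
- *That the DSMB would not see it.* Sections 9.2.4 and 9.4 give it safety data and participant safety as its focus, and nothing restricts it to AE counts. Its charter is not at hand.
- *That the number of participants can be estimated.* Assuming that 5% to 15% of 48 have such a change gives 0.05 x 48 = 2.4 to 0.15 x 48 = 7.2, and one case in an arm of 24 is 1/24 = 4.2 percentage points. The percentages have no source in the protocol, they ignore the possibly-related filter, and they would count vital signs under a paragraph that does not cover them.
- *That one arm is favoured.* The trial is double-blind, so an unclear recording rule does not by itself favour either arm. No AE rate is a listed endpoint, and the termination trigger in 8.7 is multiple SUSARs.

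**Conclusion.** The point holds as a defect in the recording rule. The conflict is explicit for laboratory changes that need new or altered treatment without stopping study drug, a group that 8.4.1 probably makes small. It is implied for other clinically significant, non-serious laboratory changes. For blood pressure and pulse there is one permissive rule and no contradiction.

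The consequence is that a clinically significant finding from a safety blood draw may go unrecorded as an AE and so outside the AE follow-up rules. SAEs and events that stop study drug remain captured. The number affected cannot be derived from the protocol. The filter in 9.2.4 limits it further, perhaps not by much, since 9.2.5 accepts a reasonable time sequence even where another explanation is possible.

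The conclusion rests on reading both paragraphs as written and on no other section overriding them. It is worth correcting because the correction is specific and nearly free.

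**What to change.** In section 9.2.1, replace the sentence on clinically significant changes in the second paragraph, together with its exception, by one recording rule that agrees with the third paragraph:

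- A laboratory, blood pressure or pulse change is an AE, graded by CTCAE v5.0 as in 9.2.6, if the investigator judges it clinically significant, if it needs new or altered treatment, if it constitutes an SAE, or if it leads to study drug being stopped.
- A change judged not clinically significant, and meeting none of the other conditions, is not an AE.
- Collection of the non-serious ones remains subject to the possibly-related rule in 9.2.4, with a cross-reference so that the two sections are read together.

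This keeps the existing treatment criterion and gives blood pressure and pulse the same rule as laboratory values. It needs a short wording change and no new measurements. The running cost is a few more AE entries.

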#### **9.2.2 Serious adverse events (SAEs)**

A serious adverse event is any untoward medical occurrence or effect that

- results in death;
- is life threatening (at the time of the event);
- requires hospitalisation or prolongation of existing inpatients' hospitalisation;
- results in persistent or significant disability or incapacity;

- is a congenital anomaly or birth defect; or
- any other important medical event that did not result in any of the outcomes listed above due to medical or surgical intervention but could have been based upon appropriate judgement by the investigator.

An elective hospital admission will not be considered as a serious adverse event.

A hospitalization meeting the regulatory definition for “serious” is any inpatient admission, regardless of the length of stay, even if as a precautionary measure for continued observation. Elective hospitalizations for the routine administration of protocol therapy, therapeutic blood products, treatment of a pre-existing condition that did not worsen from baseline, elective procedures, or for social or technical reasons are not considered SAEs. However, prolongation of hospitalization or re-admission after the individual has been discharged for reasons other than administrative, will be considered SAEs.

All SAEs that occur after any participant has been enrolled (i.e. who signed ICF), before treatment, during treatment, or within 30 days following the cessation of treatment, whether or not they are related to the study, must be recorded.

The investigator will report all SAEs to the sponsor without undue delay after obtaining knowledge of the events, except for the following SAEs:

The sponsor will report the SAEs through the web portal *ToetsingOnline* to the accredited METC that approved the protocol, within 7 days of first knowledge for SAEs that result in death or are life threatening followed by a period of maximum of 8 days to complete the initial preliminary report. All other SAEs will be reported within a period of maximum 15 days after the sponsor has first knowledge of the serious adverse events.

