##### *Patients*

- Current or history of significant alcohol consumption for a period of more than 3 consecutive months within 1 year before screening (significant alcohol consumption is defined as more than 2 international units/day for females and more than 3 international units/day for males, on average; 1 international unit contains  $\pm 14$  grams of alcohol)
- liver cirrhosis or hepatocellular carcinoma
- hepatitis B and/or C
- auto-immune hepatitis
- Wilson's disease
- primary sclerosing cholangitis
- primary biliary cholangitis
- alpha-1-antitripsine deficiency and hemochromatosis
- history of liver transplant, current placement on a liver transplant list
- use of pre-, pro- or synbiotics
- use of systemic antibiotics 3 month prior to randomization
- use of tamoxifen, methotrexate or amiodarone
- prior or planned bariatric surgery
- active GLP-1 receptor agonist treated diabetes mellitus
- bleeding disorder
- International normalized ratio (INR) of prothrombin time  $>1.4$  or platelet count  $<100 \times 10^9/L$  at screening
- anti-platelet/coagulant therapy use which cannot be temporarily discontinued
- any major cardiovascular event within 6 months prior to screening (e.g. myocardial infarction, cerebrovascular accident)
- prolonged compromised immunity (e.g. recent cytotoxic chemotherapy, HIV-infection with a CD4 count  $< 240$ )

- active or prior history of invasive malignancy (except for curatively treated in situ carcinomas [e.g., cervix] or non-melanoma skin cancer) unless a complete remission was achieved
- surgery scheduled for the trial duration period, except for minor surgical procedures, in the opinion of the investigator
- pregnant or nursing women
- any condition which, in the investigator's opinion, might jeopardize participants' safety or compliance with the protocol
- participation in another concomitant clinical trial.

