##### 8.4.1 Specific criteria for withdrawal

Participants with any new condition during the study that require hospital admission, change in drug prescriptions or likely to affect the outcome of this study will be withdrawn.

Participants will also be withdrawn if instructions as written in the protocol are not followed.

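### Section 9.2.2 gives two incompatible rules on elective admissions: some planned admissions for new or worsened conditions, and planned re-admissions, are SAEs under one rule and not under the other

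*Protocol*

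**What the plan says.** Protocol section 9.2.2 lists the usual seriousness criteria, among them an untoward occurrence that "requires hospitalisation or prolongation of existing inpatients' hospitalisation". Directly after the list stands a sentence with no condition on cause, onset or worsening: "An elective hospital admission will not be considered as a serious adverse event".

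The next paragraph starts from the opposite end. A serious hospitalisation "is any inpatient admission, regardless of the length of stay, even if as a precautionary measure for continued observation". Elective stays are then exempted by reason: routine protocol therapy, blood products, and "treatment of a pre-existing condition that did not worsen from baseline, elective procedures, or for social or technical reasons are not considered SAEs". The paragraph closes by counting as SAEs both a prolonged stay and a re-admission after discharge, unless the reason is administrative. It makes no exception for a re-admission that was planned.

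Two collection rules decide what follows from the classification. Under section 9.2.2, SAEs are recorded from consent until 30 days after treatment ends, whatever their relation to the study. Under section 9.2.4, non-serious AEs are collected only if possibly related, and only from randomisation.

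**The concern.** Investigators apply the SAE definition when an event happens, and no later analysis can repair a wrong classification if the event was never entered. With two rules in adjacent paragraphs, the same planned admission can be reported as an SAE or left out, depending on which paragraph is followed.

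Seriousness carries much of this protocol's safety machinery. It brings in an event that is judged unrelated. It triggers the 7-day or 15-day report to the ethics committee (9.2.2). It defines what is followed up after withdrawal (8.6) and which adverse events the annual progress report lists (12.4). It is also a precondition for a SUSAR, and section 8.7 ends the study when there are multiple SUSARs. Section 8.4.1 adds that "Participants with any new condition during the study that require hospital admission" are withdrawn, so some of the participants concerned would also leave the trial.

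**Working it through.** No figure in the protocol bears on this point and no formula applies. The check sets the two rules side by side and then follows an affected event through the collection rules.

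**Step 1. Classification under each rule (both in section 9.2.2).**

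| Planned inpatient admission | Unconditional sentence | Next paragraph | Result |
|---|---|---|---|
| Non-procedural care of a pre-existing condition that has worsened | Not an SAE | SAE, because the exemption is limited to conditions that have not worsened | Conflict |
| Non-procedural care of a new condition | Not an SAE | SAE, because no listed exemption fits | Conflict |
| Re-admission for a non-administrative reason | Not an SAE | SAE, by the closing sentence | Conflict |
| Elective procedure, first admission | Not an SAE | Not an SAE on the words of the list | No conflict, but no worsening qualifier |
| Pre-existing condition, unchanged | Not an SAE | Not an SAE | Agreement |
| Protocol therapy, blood products, social or technical reasons | Not an SAE | Not an SAE | Agreement |

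If the unconditional sentence governs, the worsening qualifier has no effect, and the re-admission sentence has none for planned re-admissions. The conflict is confined to the first three rows. The fourth row is a separate gap: one item in the list is conditional on no worsening and the item on procedures is not, so a procedure for a condition that began or worsened on study is exempt either way.

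**Step 2. An event from the first three rows, classified by the unconditional sentence.**

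- It loses SAE status unless it meets another criterion, such as being life-threatening or an important medical event.
- If it is judged possibly related and occurs after randomisation, section 9.2.4 collects it as a non-serious AE. It is then in the data, but in the wrong class, and it cannot count as a SUSAR.
- If it is judged unrelated, or occurs between consent and randomisation, section 9.2.4 does not call for it.

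**Step 3. What else could catch it.**

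- Section 9.2.1 requires AEs that lead to stopping study drug to be recorded, with no condition on relatedness. The sentence sits among text on laboratory values and vital signs, so its reach is arguable.
- Section 8.6 follows participants withdrawn for medical reasons until the condition resolves or stabilises.
- Section 9.2.5 sets a low bar for possible relatedness: a reasonable time sequence is enough even where another explanation exists. With daily dosing for 24 weeks, many new conditions would clear it.

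Some affected events would therefore be captured in some form, though none of these routes restores SAE status.

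**The case against.** The strongest reply is that the second paragraph merely spells out the short sentence before it, so a sensible investigator would apply the list. That is a possible reading, but the protocol does not state it. The short sentence is unqualified, and a reader who stops there has followed the text.

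A second reply is that the conflict is narrow, and that is right. A reader might infer that elective surgery is the main example, since section 4.3 excludes patients with "surgery scheduled for the trial duration period, except for minor surgical procedures, in the opinion of the investigator", and non-minor surgery that still occurs would mostly have been planned after entry. The documents do not support using this as a contradiction, because both rules exempt elective procedures. It bears only on the missing qualifier in the list.

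A third reply concerns the consequence. A reader might infer that such an event would appear in no safety table at all. Sections 8.6, 9.2.1 and 9.2.5 do not allow so firm a statement: the event may be missed, but some will be caught. Nor do the documents say that admission is usually the only seriousness criterion met.

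The last reply is that nothing here touches the primary endpoint, the sample size or the randomisation, and nothing points to a difference between arms. That stands, and it limits the weight of the point.

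**Conclusion.** Section 9.2.2 contradicts itself for planned non-procedural admissions for a new or worsened condition and for planned re-admissions. Separately, its list exempts elective procedures without asking whether the underlying condition arose or worsened on study. Under the unconditional sentence, the affected events lose SAE status unless another criterion applies, and some may go uncollected.

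The size cannot be estimated, because the protocol gives no hospitalisation rate. A reader might assume that 5% to 15% of the 48 participants are admitted for a new or worsened condition and that 30% to 50% of those admissions are planned, which gives 48 × 0.05 × 0.30 = 0.72 to 48 × 0.15 × 0.50 = 3.60 events. Both rates are assumptions with no basis in the document. The product also counts procedures that both rules exempt, events that qualify on other criteria, and events that an investigator would classify by the list. For those rates it is a ceiling, not an estimate of lost SAEs. With 48 participants over 24 weeks and so narrow a class of admission, the true number is probably small. The point deserves correction because it concerns the definition of a serious event and is cheap to settle.

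**What to change.** Delete the unconditional sentence in section 9.2.2 so that the reason-based list alone governs elective admissions. In the list, tie *elective procedures* to the qualifier already used for pre-existing conditions: exempt a procedure only if it was planned before consent or is for a condition that has not worsened since baseline. Then state the result plainly: an untoward medical occurrence that arises or worsens after consent and leads to inpatient admission is an SAE, whether or not the admission was planned.

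The new text should keep the requirement of an untoward occurrence. Making every remaining inpatient admission an SAE would go too far, since it would take in admissions arranged after consent with no adverse event behind them.

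The cost is a change of wording in one section, a matching line on the SAE form, and a few more SAE reports.
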